**Fig. 3 Fig3:**
[figure not shown]
Consort flow diagram

**Fig. 4 Fig4:**
[figure not shown]
SPIRIT flowchart of the schedule of enrolment, intervention, and assessments

##### The 6-month RCT

During the 6-month RCT period, the intervention group will complete the health school (2 months) and start regular Hans Kai group meetings (6 months). During this period, the intervention group participants will complete the MHC-SF at the end of the health school and 3 months after the end of the health school, as well as all physical and mental health assessments 6 months after the end of the health school. During the 6-month RCT period, the control group will have access to standard care and will complete the MHCF-SF (3 months after enrollment) as well as all physical and mental health assessments (6 months after enrollment). In both groups, the primary outcome mental health, measured via the MHC-SF, will be assessed at baseline as well as at the 3-month and 6-month timepoints.

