### Randomized controlled trial

#### Study design

The experimental component of the mixed methods RCT will follow a 6-month 2-group parallel superiority design, with a 12–18-month observational follow-up (see Fig. 2 for details). There will be a 2:1 allocation of participants to the intervention versus the control group. The control group will consist of 6 months of standard care that adults can access in the Canadian Province of Manitoba, including any services and programs that are offered at NorWest, except Hans Kai. At the end of the 6-month control period, the control group participants will be offered the opportunity to join Hans Kai and, once in the intervention, they will be followed for up to 18 months. The participants in the intervention group will be followed for a minimum of 6 months (RCT period) and up to 18 months; however, the randomized controlled portion of the study will last for the first 6 months, while the observational follow-up for them will last 12 months. After baseline, there will be a 2-month period of Hans Kai program implementation during which program participants will attend the Hans Kai Health School, prior to starting regular group meetings.

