#### Procedure

At the baseline assessment, all participants (both the intervention and control group) will undergo a clinical exam that will be performed by a trained research team member, who will measure participants’ blood glucose levels, blood pressure, weight, and waist circumference according to provincial health standard protocols. All clinical measurements will be taken three times, except blood glucose, which will be measured only once using a glucometer that tests capillary blood samples taken by finger prick sampling. Blood pressure will be measured in triplicate following 10 min of acclimatization to the measurement room, with a 2-min break between measurements. The average of the three assessments will be used as measure of blood pressure. Following the clinical assessment, participants will be asked to complete all self-report measures, including a sociodemographic questionnaire, the MHC-SF, the Revised UCLA Loneliness Scale, the PHCS, the Adapted Healthy Eating Assessment, and the PSQI. Fitbits will also be used to objectively assess changes in participants’ physical activity as well as sleep quality and patterns. Participants will be shown by the study staff how to wear the Fitbit and will be given basic instructions on its use. Study participants will be asked to wear the Fitbit for 7 complete days on the assessment week, including when they are asleep so that their sleep quality and patterns can be recorded.

Following the baseline assessment, study participants will be randomly assigned to either the intervention group or the control group (see Fig. 3 for Consort flow diagram) [36]. After random allocation to either trial condition, participants in the intervention group will immediately enter the Hans Kai program, while participants in the control group will be exposed to 6 months of standard care. Participants who are randomized to the control group will receive $100 CAD (made out in two payments of $50 CAD, one at the 3-month visit and one at 6-month visit). This remuneration for participants who are randomly assigned to the control group instead of the intervention group will be used as a strategy to improve adherence to the intervention protocol. We will also monitor adherence by tracking attendance to the health school and trial visits. See Fig. 4 for the SPIRIT flowchart of the schedule of enrollment, intervention, and assessments.

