##### The follow-up observational study

The follow-up observational study will last a total of 18 months for the control group and 12 months for the intervention group. The participants coming from the control group will first complete the Hans Kai health school (2 months) and then in the first 6 months of the follow-up study, they will complete the same visits that were completed by the intervention group during the 6-month RCT period, followed by two full assessments, including all physical and mental health measures that will be performed 6 months apart (12 additional follow-up months). During the follow-up study, the participants coming from the intervention group will complete two full assessments, including all physical and mental health measures that will be performed 6 months apart.

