#### Statistical analysis

Preliminary analysis will involve computing descriptive statistics for all quantitative variables. For continuous variables, means, standard deviations, and quartiles will be estimated, while categorical variables will be summarized with counts and percentages in each category. Summaries will be performed by group and by assessment, as well as for the entire study group. Primary data analysis of the RCT portion will involve comparing the mean values of the within-subject changes in outcome variables from baseline to 6 months between the treatment and control groups. Secondary data analysis will include a test of the interaction between time in the Hans Kai program and the outcome measurements in all participants from 0 to 20 months. The primary analysis will be conducted at the 0.05 level of significance. In general, test results will be described as significant if their *p*-values are less than 0.05 without adjustments for multiple inference. Multiple imputation will be used to deal with missing data.

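### RCT visits are anchored differently by arm (about 8 months after baseline against 6 at the primary endpoint), contradicting the common 3- and 6-month timepoints stated elsewhere

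*Protocol article*

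**What the plan says.** **When the intervention starts.** Under Procedure, "participants in the intervention group will immediately enter the Hans Kai program, while participants in the control group will be exposed to 6 months of" usual care. Study design adds: "After baseline, there will be a 2-month period of Hans Kai program implementation", which is the health school.

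**Visit anchors, section The 6-month RCT.** Intervention participants complete the MHC-SF when the school ends and again 3 months later. They then complete everything, "as well as all physical and mental health assessments 6 months after the end of the health school". Control participants complete the MHC-SF 3 months after enrolment and "all physical and mental health assessments (6 months after enrollment").

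**Statements that point to common timing.**
- The 6-month RCT closes by saying that both groups have the MHC-SF at baseline, 3 months and 6 months.
- Study design: "the randomized controlled portion of the study will last for the first 6 months".
- Statistical analysis defines the primary contrast as "comparing the mean values of the within-subject changes in outcome variables from baseline to 6 months between the treatment and control groups".
- Table 1 schedules the non-primary outcomes at baseline and then at 6-month intervals of the programme or of standard care. The description of the programme makes the school its first phase.
- The qualitative section (explanatory sequential component) equates the 12-month follow-up with one year after enrolling in the programme.

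**The concern.** A randomised comparison of change scores isolates the programme only if both arms are observed over the same interval. Here one arm's clock appears to start when the school ends and the other's at enrolment, yet both visits carry the 6-month label. Staff following the visit description would measure the intervention arm about two months later. Season, external events or any other drift in wellbeing would then have longer to act in that arm. This affects the primary MHC-SF contrast, the interim MHC-SF and every other outcome collected at the final trial visit. It is a matter of how the visits are scheduled, so it is best settled before primary visits take place.

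**Working it through.** **Step 1. Visit times from baseline.** Inputs: school length 2 months, starting after baseline (Study design; Procedure); visit anchors (The 6-month RCT).

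| Visit | Intervention | Control | Gap |
|---|---|---|---|
| Baseline | 0 | 0 | 0 |
| End of school | 2 | none | n/a |
| Labelled 3-month | 2 + 3 = 5 | 3 | 2 months |
| Labelled 6-month | 2 + 6 = 8 | 6 | 2 months |

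No post-baseline visit coincides between arms.

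**Step 2. Is the 8-month reading an isolated phrase?** Three things fit it.
- The 6-month RCT section places 2 months of school and 6 months of group meetings inside the one trial period, which makes 8.
- The follow-up section sends former controls through the school first, and then through 6 months of the visits that the intervention arm had.
- Statistical analysis uses a span of 0 to 20 months in the programme, and 2 + 6 + 12 = 20.

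The count of four intervention visits against three control visits does not discriminate. Months 0, 2, 5 and 8 make four, but so would months 0, 2, 3 and 6.

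**Step 3. The plan's own power figures (Sample size).** Inputs: SD of change 5, 60 against 30 analysed, two-sided alpha 0.05 (two-sidedness inferred from the ± difference).
- SE = 5 × √(1/60 + 1/30) = 1.118.
- Detectable difference at 80% power = (1.960 + 0.842) × 1.118 = 3.13 (3.17 with the t distribution), against 3.1 stated.
- Power at 3.1 is 79.2% (normal) or 78.3% (t).
- With 10 groups against 30 controls, the detectable difference is 5.11 (normal) or 5.25 (t), against 5.2 stated.

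Both figures reproduce, and visit timing does not enter them.

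**Step 4. What two extra months could do.** The documents give no drift rate, so d below is an assumption. If MHC-SF drifts by d points per month whatever the arm, the contrast shifts by (8 − 6) × d = 2d. The last column is the two-sided t-test rejection rate with no programme effect (60 against 30, SD 5).

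| d (points/month) | Shift 2d | Share of 3.1 | Rejection rate |
|---|---|---|---|
| 0 | 0 | 0% | 5.0% |
| 0.1 | 0.2 | 6% | 5.4% |
| 0.25 | 0.5 | 16% | 7.3% |
| 0.5 | 1.0 | 32% | 14.3% |
| 1.0 | 2.0 | 65% | 42.5% |

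**The case against.** **The article also states the right design.** Several sections give a common 6-month timepoint, and Figures 2 and 4 and Supplementary Table 1, which should carry the schedule, could not be checked. This stands in part. It cannot be said as fact that the intervention arm will be measured at month 8; what can be said is that the text conflicts. A consistent figure would still leave the visit description to be corrected.

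**Elapsed time may not matter much.** Regression to the mean need not build up with time, and eligibility sets no MHC-SF threshold. Practice effects depend mainly on the number of administrations, which differs between arms (four visits against three) and would not be cured by aligning the last visit. Seasonal effects depend on an enrolment calendar that is not given. All this stands, and it is why the size of any bias is left open.

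**Analysis could interpolate.** The intervention MHC-SF at months 5 and 8 could be interpolated to month 6. That needs an assumed trajectory shape, and it is not available for outcomes collected only at baseline and the final trial visit.

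**Stronger readings that a reader might infer, and that the documents do not support:**
- *That the follow-up length is an arithmetic slip.* The article says "The follow-up observational study will last a total of 18 months for the control group and 12 months for the intervention group", while the components for former controls add to 2 + 6 + 12 = 20. But the wording allows a clock that starts after the school, giving 6 + 12 = 18, with 20 as the same span including the school. The clock origin is unstated; the sum need not be wrong.
- *That crossover contaminates the primary endpoint.* Controls are offered the programme at the end of their 6-month period, and their primary value is taken at 6 months, so it is not exposed.
- *That the bias is about 2.2 points, or 70% of the detectable difference.* That figure treats the whole +6.5 change in the earlier cohort as linear non-programme drift (6.5 / 6 × 2 = 2.17; 2.17 / 3.1 = 0.70). Nothing in the article supports that attribution.

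**Conclusion.** The inconsistency is real and concerns the primary endpoint. Taken as written, the visit anchors put the final trial assessment at about 8 months in the intervention arm and 6 in the control arm, with the same 2-month gap at the interim. This rests on the school lasting 2 months and starting promptly after randomisation, both of which the article states.

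Whether bias follows depends on two things the article does not settle: which of its conflicting statements is carried out, and whether MHC-SF changes with time for reasons other than the programme. The tabulated shifts are hypothetical, and the direction could be either way. The defect still has to be corrected, because following the visit description would confound arm with elapsed time and later analysis could not fully undo that.

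**What to change.** 1. Measure the interim and primary MHC-SF, and the other RCT outcomes, at the same time since randomisation in both arms and before controls are offered the programme. Two schedules achieve this, and the choice is the investigators':
   - *Six months after randomisation in both arms.* This matches Study design and Statistical analysis. The cost is that the intervention arm will have had about 6 − 2 = 4 months of group meetings at the endpoint.
   - *A common later visit, with control crossover after it.* This keeps a longer meeting period at the endpoint. The cost is a longer control period, and the 6-month wording and control payment schedule would have to be revised to match.
2. Treat any intervention visit timed from the end of the school that has no matching control visit as a separate, non-primary assessment.
3. Reconcile Study design, Table 1, The 6-month RCT, Statistical analysis and the qualitative definition of the 12-month follow-up. State the clock origin for the 18- and 20-month figures, and check Figures 2 and 4 and Supplementary Table 1 against the result.

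This takes a protocol amendment and revised visit windows in REDCap. The number of participants and the stated power are unchanged. The extra MHC-SF administration in the intervention arm remains unless the end-of-school visit is also matched in controls.

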##### The follow-up observational study

The follow-up observational study will last a total of 18 months for the control group and 12 months for the intervention group. The participants coming from the control group will first complete the Hans Kai health school (2 months) and then in the first 6 months of the follow-up study, they will complete the same visits that were completed by the intervention group during the 6-month RCT period, followed by two full assessments, including all physical and mental health measures that will be performed 6 months apart (12 additional follow-up months). During the follow-up study, the participants coming from the intervention group will complete two full assessments, including all physical and mental health measures that will be performed 6 months apart.

#### Statistical analysis

Preliminary analysis will involve computing descriptive statistics for all quantitative variables. For continuous variables, means, standard deviations, and quartiles will be estimated, while categorical variables will be summarized with counts and percentages in each category. Summaries will be performed by group and by assessment, as well as for the entire study group. Primary data analysis of the RCT portion will involve comparing the mean values of the within-subject changes in outcome variables from baseline to 6 months between the treatment and control groups. Secondary data analysis will include a test of the interaction between time in the Hans Kai program and the outcome measurements in all participants from 0 to 20 months. The primary analysis will be conducted at the 0.05 level of significance. In general, test results will be described as significant if their *p*-values are less than 0.05 without adjustments for multiple inference. Multiple imputation will be used to deal with missing data.

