#### Sample size

The primary analysis will be performed based on the pre- to post-intervention changes in the primary outcome, the Mental Health Continuum Short Form (MHC-SF) [23], comparing the mean change scores between the intervention and control participants, with a nested design to account for participant group membership in Hans Kai [24]. Based on data from previous studies [4, 24] and the RCT study design, we expect the changes from baseline MHC-SF scores within each subject group to be approximately normally distributed with a standard deviation of 5. The average within-group pre-post changes in MHC-SF scores in the Hans Kai prospective cohort study were + 6.5 in 34 participants at 6 months [18]. With a planned sample size that accounts for dropouts of 90 adults, with 60 intervention participants and 30 control participants, we would have a power of 80% to detect a true difference in the mean response of intervention and control participants of − 3.1 or 3.1 at the end of the 6-month RCT component [25]. This scenario assumes that the outcomes of each participant will be independent of the Hans Kai peer group they join. However, since part of the Hans Kai program includes forming groups, a very conservative power calculation considers the “effective” sample size for the Hans Kai program to be equal to the number of groups rather than the number of participants. We anticipate that 60 intervention participants will form 10 independent groups of six participants per group. In this very conservative scenario, with 10 groups in the intervention arm and 30 control participants, we would be able to detect a true difference in the mean scores of intervention and control participants of − 5.2 or 5.2 with 80% power. We believe that the actual study power will fall somewhere between the two scenarios presented here. With a starting sample size of 105 adults and an estimated 15% dropout rate during the study period [18], we expect to generate a minimum sample of approximately 90 participants at the 18-month follow-up.

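### The Statistical analysis section leaves out the peer-group nesting that the Sample size section gives the primary analysis, and nothing extends it to the secondary and tertiary outcomes

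*Protocol article*

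**What the plan says.** The protocol article describes the main RCT comparison in two places.

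- **Sample size.** The primary analysis of the MHC-SF is described as "comparing the mean change scores between the intervention and control participants, with a nested design to account for participant group membership in Hans Kai". The section adds: "We anticipate that 60 intervention participants will form 10 independent groups of six participants per group". It gives a detectable difference of 3.1 if participants are independent of their peer group and 5.2 if each group counts as one unit. It expects the real power to lie between these two cases.
- **Statistical analysis.** The primary analysis of the RCT portion is described as "comparing the mean values of the within-subject changes in outcome variables from baseline to 6 months between the treatment and control groups". The section then says: "The primary analysis will be conducted at the 0.05 level of significance". Other results are called significant below 0.05 with no multiplicity adjustment. Nesting, clusters and peer groups are not mentioned, and no test or model is named.

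The section on the Hans Kai program names social connection and peer support within groups as the way the programme is thought to work. Controls receive standard care and form no Hans Kai groups during the six months. The Blinding section says that the statistician and the data management team are blinded to allocation during analysis.

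**The concern.** If peer support is the active ingredient, members of one group will tend to change together. Intervention outcomes are then correlated within groups while control outcomes are independent, which is a partially nested design. The Sample size section recognises this; the section that sets out the analysis does not carry it over.

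The gap matters most for the secondary and tertiary outcomes: loneliness, health competence, health behaviours and cardiometabolic measures. The nesting statement is tied to the MHC-SF, so for these outcomes the unqualified comparison of mean changes is the only analysis text.

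A comparison that ignores positive within-group correlation understates the variance of the intervention mean. Confidence intervals come out too narrow and the error favours a false positive for the programme. Two descriptions of one analysis also leave a choice that could be made after the data are seen.

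**Working it through.** **Inputs from the article**

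- Level 0.05 (Statistical analysis). Sidedness is not stated in words. Two-sided is inferred because the detectable difference is given with both signs: "or 3.1 at the end of the 6-month RCT component".
- Analysed sample: "with 60 intervention participants and 30 control participants" (Sample size).
- Change scores expected "to be approximately normally distributed with a standard deviation of 5" (Sample size).
- Power: "we would have a power of 80% to detect a true difference in the mean response of intervention and control participants of" 3.1 in either direction (Sample size).
- Ten groups of six in the intervention arm (Sample size).

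**Assumption.** The article gives no ICC. Values of 0.05, 0.10 and 0.20 are used for illustration, with smaller values shown for contrast.

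**Step 1: reproduce the plan's figures.** The detectable difference is (1.960 + 0.842) × SE.

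- Independent participants: SE = 5 × √(1/60 + 1/30) = 1.118, so the difference is 3.13 (3.17 with the t distribution). The plan says 3.1.
- Groups as units: SE = 5 × √(1/10 + 1/30) = 1.826, so the difference is 5.11 (5.25 with the t distribution). The plan says 5.2.

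Both figures reproduce.

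**Step 2: type I error of an unadjusted test when only the intervention arm is clustered.** With groups of six the design effect in that arm is 1 + 5 × ICC. The ratio of true to naive standard error is

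r = √{[(1 + 5 × ICC)/60 + 1/30] / [1/60 + 1/30]}

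and the true two-sided level is 2 × [1 − Φ(1.96/r)].

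At ICC 0.10, for example, r = √[(1.5/60 + 1/30)/0.05] = √1.167 = 1.080. Then 1.96/1.080 = 1.815, and the level is 0.070.

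| ICC (assumed) | Design effect | r | Level, formula | Level, simulated |
|---|---|---|---|---|
| 0 | 1.00 | 1.000 | 0.050 | 0.050 |
| 0.01 | 1.05 | 1.008 | 0.052 | 0.052 |
| 0.02 | 1.10 | 1.017 | 0.054 | 0.054 |
| 0.05 | 1.25 | 1.041 | 0.060 | 0.059 |
| 0.10 | 1.50 | 1.080 | 0.070 | 0.070 |
| 0.20 | 2.00 | 1.155 | 0.090 | 0.091 |

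The simulated column is a pooled t-test on 100,000 simulated trials per ICC, with 10 groups of six against 30 independent controls.

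**Step 3: does respecting the nesting restore the level?** In the same simulations, 10 group means were compared with 30 individual controls using Welch–Satterthwaite degrees of freedom. The level was 0.049 to 0.051 for every ICC from 0 to 1. This is a simple stand-in for the mixed model with equal group sizes; the mixed model itself was not simulated.

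**Step 4: what the nesting costs in detectable difference.** This is 2.802 × 1.118 × r (normal approximation): 3.26 at ICC 0.05, 3.38 at 0.10 and 3.62 at 0.20, against 3.13 under independence.

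**The case against.** The strongest reply is that the two sections are compatible. The Sample size section states the nesting outright, and the Statistical analysis section can be read as a shortened restatement of the same comparison. It names no test and nowhere says that participants will be treated as independent. The article also condenses a fuller protocol that is available on request, and a separate analysis plan may give the model.

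Much of this stands. A reader might infer that the plan commits to an unclustered test, so that the 0.05 level fails. The document does not support that. For the primary outcome the nested design is on record. The inflation needs both an unadjusted test and a positive ICC, and at ICCs of 0.01 to 0.02 it is small (5.2% to 5.4%).

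Larger figures are also tempting, but they are not the planned case. The programme in general allows groups of 5 to 30, yet this trial plans groups of six. An ICC of 1 would give about 23% by the formula (25% simulated), but that is the extreme the protocol itself presents as very conservative.

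The reply fails on one point. Reading the Statistical analysis section as shorthand rescues only the MHC-SF. The nesting statement does not cover the secondary and tertiary outcomes. Nor is this a request for detail normally left to an analysis plan: the article states the design feature in one section and omits it from the section on the analysis.

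**Conclusion.** The point holds as a mismatch within the article. The nested design is stated for the primary MHC-SF analysis in the Sample size section, is absent from the Statistical analysis section, and is not extended to the other RCT outcomes.

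The consequence is conditional. If the comparison is run unadjusted, with 10 groups of six against 30 controls and equal total variance in both arms, the two-sided level is about 6% to 9% for assumed ICCs of 0.05 to 0.20. It is 5% if the nesting is respected or the ICC is zero. The ICC range is an assumption, although the protocol itself expects the truth to lie between no clustering and complete clustering.

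**What to change.** In the Statistical analysis section, carry over the nested design and state that it applies to every RCT outcome. A suitable form is a partially nested linear mixed model with a random effect for Hans Kai group in the intervention arm only, controls as singletons, and Satterthwaite or Kenward–Roger degrees of freedom, since only about 10 groups are expected. Intervention participants who never join a group can also be treated as singletons.

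Costs:

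- **Precision.** At ICCs of 0.05 to 0.20 the standard error grows by about 4% to 15% (r above), before the small-sample degrees of freedom widen intervals a little further. The detectable difference becomes about 3.3 to 3.6, inside the 3.1 to 5.2 range that the Sample size section already accepts.
- **Data.** Groups form only after the health school, and the article does not say that a group identifier enters the trial dataset. It must be recorded.
- **Blinding.** Clustering in one arm only can show the statistician which arm is which. The model should therefore be fixed before the data are seen, and the limit on blinding acknowledged.
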